### Statistical analysis

All analyses will be carried out using Stata [60]. In accordance with Consolidated Standards of Reporting Trials (CONSORT) guidelines, we will report all participant flow. Descriptive statistics of recruitment, dropout and completeness of interventions will be provided.

The main efficacy analysis will be via intention-to-treat including all participants, with no planned interim analysis for efficacy or futility. Baseline characteristics will be presented by randomised group without formal statistical tests. We will test the primary hypothesis for between-group change in the primary outcomes at 8 weeks using analysis of covariance with baseline outcome measure and treatment assignment as fixed effects, and apply standard regression diagnostics. The analysis will use statistical techniques for handling missing outcome data under a missing-at-random assumption. The secondary outcomes will be analysed using an analogous method, as will subsequent measures of the primary outcomes at 24 weeks. Analysis of all treatment effects will be undertaken after all 24-week outcome measures are completed.

We will use modern causal inference methods to investigate the mediation hypothesis [61]. If the efficacy analysis shows significant between-group differences in the SCI at 4 and 8 weeks, then we will use parametric regression models to test for the indirect effect of SCI on outcomes, and the residual direct effect of treatment on outcomes at 8 and 24 weeks respectively. Since all the measures are continuous, the indirect effects are calculated by multiplying relevant pathways and bootstrapping is used to produce valid standard errors for the indirect effects. All analyses will adjust for baseline measures of the SCI, outcomes and putative measured confounders. Mediation analyses are potentially biased by measurement error in mediators and hidden confounding between mediators and outcomes and we will investigate the sensitivity of the estimates to these problems.

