## Methods/design

### Research design

The study is a parallel-group, superiority, RCT of dCBT (+ treatment as usual, TAU) versus SHE (+TAU). The trial design is summarised in Fig. 1. The study will be carried out completely online. Participants will access the screening assessment, participant information statement, informed consent form, allocation to condition and intervention, and baseline and follow-up assessments via web or mobile platforms (see also Additional files 1 and 2). Participants will be able to print a copy of the participant information statement and will have the opportunity to contact the researchers via phone or email before consenting. The study has received ethical approval from the University of Oxford Medical Sciences Inter-Divisional Ethics Committee (ref MS-IDREC-C2-2015-024) and is registered at ISCRTN (ISRCTN60530898).

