### Randomisation and allocation concealment

This study will use simple randomisation with an allocation ratio of 1:1, as recommended for large clinical trials [36]. It will be carried out by the automated online system. Hence the research team will be unable to influence randomisation, and will have no access to future allocations.

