### Sample size calculation

Our planned primary intention-to-treat analyses will compare dCBT + TAU versus SHE + TAU for each of the three primary outcomes separately. Assuming a significance level of 1.667 % (adjusted from 5 % because of having three primary outcomes) and a power of 90 %, to detect a standardised effect size of 0.25 we require a minimum of 433 participants in each of the groups in the analysis. Accounting for a conservative dropout rate of 13 %, we will recruit 500 participants in each treatment group, or 1000 participants in all. This sample size will have more than 80 % power to detect a large-sized indirect effect through the sleep mediator (proportion mediated approximately 75 %) for each between-group comparison. We believe that a sample of this size is feasible to recruit for two reasons. First, online/mobile interventions are much more accessible than in person interventions; and second, published research using dCBT has already shown that large samples may be recruited over comparatively short recruitment periods.

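### The primary ANCOVA lists only the outcome's own baseline and treatment; adding baseline SCI and the other two primary baselines would give a small gain in precision at almost no cost

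*Protocol article*

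**What the plan says.** The Statistical analysis section of the protocol article names the terms of the primary 8-week model: "analysis of covariance with baseline outcome measure and treatment assignment as fixed effects". Secondary outcomes and the 24-week primary measures are to be analysed analogously. The word 'only' does not appear, but the terms are listed and no other covariate is named for the efficacy comparison.

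The same paragraph commits to "statistical techniques for handling missing outcome data under a missing-at-random assumption". It does not name the technique or its auxiliary variables.

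The following paragraph, on mediation, says: "All analyses will adjust for baseline measures of the SCI, outcomes and putative measured confounders". In context this refers to the mediation analyses.

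The Participants section makes an SCI score of 16 or less an entry criterion, and the Assessment points section places a baseline assessment at week 0. Allocation uses "simple randomisation with an allocation ratio of 1:1", so there is no stratification factor that the model would have to carry.

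**The concern.** The three primary outcomes are all self-reported aspects of health and well-being in people with insomnia. Baseline insomnia severity and the other two primary measures may therefore predict each outcome beyond its own baseline. In a randomised linear comparison of about 870 analysed participants, a few prespecified prognostic covariates do not bias the treatment effect, and any variance they explain narrows the interval. The data are collected in any case.

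A second, conditional benefit concerns missing outcomes. One arm has six sessions and daily diaries; the other has a website and a booklet. If completion depends on insomnia severity differently in the two arms, an analysis that conditions on baseline SCI rests on a more believable missing-at-random assumption than one that does not.

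At stake is a modest improvement in the primary analysis. Its validity is not in question.

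**Working it through.** **Inputs from the article.** Significance level: "Assuming a significance level of 1.667 % (adjusted from 5 % because of having three primary outcomes". Power is 90%. Effect and size: "to detect a standardised effect size of 0.25 we require a minimum of 433 participants in each of the groups in the analysis". Loss: "Accounting for a conservative dropout rate of 13 %, we will recruit 500 participants in each treatment group". Sidedness is not stated; the two-sided calculation is the one that reproduces the article's number.

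**Inputs assumed, because the article gives none.** Correlation r of each outcome with its own baseline: 0.3-0.7. Extra share p of the residual variance explained by the added baselines (partial R²): 0.01-0.10.

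**Step 1: reproduce the stated size.** n per arm = 2(z₁₋α/₂ + z₀.₉)²/d² = 2(2.394 + 1.282)²/0.25² = 432.3, so 433, as stated. A one-sided test would give 372. Dropout: 433/0.87 = 497.7, so 498, rounded to 500; 500 × 0.87 = 435 analysed per arm. Power at 433 is 0.9005. The calculation takes no credit for any covariate.

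**Step 2: effect on the standard error.** Added covariates multiply the standard error by √(1 − p): 0.995, 0.990, 0.975 and 0.949 for p = 0.01, 0.02, 0.05 and 0.10. That is a reduction of about 0.5-5%. In sample-size terms, 870/(1 − p) − 870 is about 9 participants at p = 0.01 and 97 at p = 0.10.

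**Step 3: effect on power at 0.25, with 433 per arm.** Power = Φ(d/(σ√(2/n)) − z₁₋α/₂), with σ² = (1 − r²)(1 − p).

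| Own-baseline r | p = 0 | p = 0.01 | p = 0.02 | p = 0.05 | p = 0.10 |
|---|---|---|---|---|---|
| no credit | 0.9005 | 0.9037 | 0.9069 | 0.9162 | 0.9310 |
| 0.3 | 0.9282 | 0.9308 | 0.9334 | 0.9409 | 0.9526 |
| 0.5 | 0.9681 | 0.9696 | 0.9711 | 0.9752 | 0.9814 |
| 0.7 | 0.9971 | 0.9973 | 0.9975 | 0.9981 | 0.9988 |

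The gain over p = 0 is about 0.3-3 points with no own-baseline credit and about 0.2-1.3 points at r = 0.5.

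**Step 4: a smaller true effect.** At 0.20, r = 0.5 and 435 per arm, power is 84.4%, rising to 85.2%, 86.4% and 88.4% for p = 0.02, 0.05 and 0.10.

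**Step 5: is 1-10% a reasonable range?** Take r = 0.5 and three added baselines that each correlate 0.3 with the outcome. If all baselines correlate 0.3, 0.4, 0.5 or 0.6 with one another, p is 6.8%, 3.0%, 0.8% or 0.0%. If the added baselines correlate 0.4 with the outcome, p is 18.8%, 12.1%, 7.2% or 3.6%. The range is plausible, but the gain could be close to nil.

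**Step 6: missing outcomes, for an observed-case ANCOVA only.** Simulation assumptions: true effect 0.25, r = 0.5, dropout depending on baseline SCI in the dCBT arm only (log-odds 0.3-0.6 per SD), partial correlation of SCI with outcome 0.1-0.3. At the planned 13% loss, the model without SCI gives about 0.228-0.249, so at worst 8-9% low. At an assumed 27% loss it gives about 0.212-0.244. Adding SCI returns 0.249-0.252 throughout. With the dropout direction reversed the estimate is too high instead, up to 0.272 at 13% loss. With the same SCI-dependent dropout in both arms there is no bias (0.250 at 27% loss).

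**The case against.** The case for leaving the model alone is that ANCOVA on the outcome's own baseline is standard, the dominant covariate is already included, and SCI has a restricted range because of the entry threshold. The trial is sized without covariate credit, so 90% power is secure. All of this stands, and it is why the point is a suggestion and not an error.

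Two stronger readings are tempting, and the article supports neither.

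*That protection against missing data is given away.* A reader might infer this from the single baseline in the model. But the article plans a missing-at-random technique, not an observed-case analysis. Multiple imputation, for example, could use baseline SCI as an auxiliary variable without its being an ANCOVA term. The technique is commonly left to a fuller document. The biases in Step 6 apply only if SCI is used nowhere, and they need dropout tied to SCI differently by arm, which the article does not report.

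*That the total effect and the mediation decomposition are inconsistent.* Sleep mediation is a primary hypothesis, so a reader might want one covariate set throughout. But under randomisation both linear models target the same total effect and differ only by sampling variation. The wider adjustment in the mediation models addresses confounding of mediator and outcome, which the randomised comparison does not face. Identical covariates would not guarantee identical totals either, since mediation also needs SCI during treatment and the analysed samples may differ. Forcing one set would remove confounders from the mediation models or load them into the primary one.

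**Conclusion.** The point holds as an optional efficiency improvement. The stated model is valid, the sample size reproduces, and no figure in the article changes. Adding baseline SCI and the other two primary baselines would shorten the standard error by about 0.5-5%. Power at 0.25 would rise by about 0.2-1.3 points if r = 0.5, or 0.3-3 points with no own-baseline credit. Both ranges rest on the assumed 1-10% of extra variance explained. The missing-data benefit is real only if dropout depends on insomnia severity differently by arm and the chosen technique does not already condition on SCI.

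**What to change.** In the Statistical analysis section, prespecify the primary 8-week ANCOVA with treatment arm, the outcome's own baseline, baseline SCI and the baselines of the other two primary measures. Carry the additional baselines into the analogous 24-week and secondary models, and state for secondary outcomes which primary baselines enter. Leave the additional confounder adjustment in the mediation models unchanged.

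The cost is one sentence, fixed before any outcome data are analysed. No new data are needed, and the primary model loses three degrees of freedom out of roughly 870.

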### Dissemination policy

Results from this study will be published in peer-reviewed scientific papers, and presented at major national and international clinical scientific meetings. Findings, wherever possible, will be made accessible online, dependent upon journal policies.

## Discussion

It is already well-established that CBT is the treatment of first choice for people with chronic insomnia, and that sleep-related outcomes, whether on index measures of insomnia or on derivations from sleep diaries, show sustained improvement [19–21]. A recent definitive placebo-controlled RCT has also demonstrated that dCBT yields effect sizes that mirror conventionally delivered face-to-face therapy [34]. What is yet to be established is whether or not CBT for insomnia is causally associated with changes in functional health, quality of life and psychological well-being. This is crucial for two reasons. First, a diagnosis of insomnia disorder cannot be made unless there are clear attributed daytime consequences of night-time poor sleep; and second, it is the degradation of people’s lived experience and quality of life that often leads to clinical complaint and help-seeking behaviour. An investigation of such as primary outcomes is long overdue. This study will be the first specifically designed investigation of the health and well-being benefits of CBT for insomnia, and the first large-scale test of the relationship between CBT-mediated sleep improvement and health status. The results can be expected to influence care provision for the 10–12 % of the adult population who have persistent insomnia problems. In particular, the results may indicate that sleep is a novel therapeutic target in relation to generalised health benefit and improved quality of life. Moreover, because we will be using a dCBT approach, a scalable solution to insomnia may be demonstrated as both viable and effective.

## Trial status

Recruitment will begin in December 2015. It is anticipated that recruitment will be complete in Summer 2016. Therefore, trial results will become available in late 2016.

## Abbreviations

CBT, cognitive behavioural therapy; CFS, Cognitive Failures Questionnaire; CI, Chief Investigator; dCBT, digital cognitive behavioural therapy; DSM-5, Diagnostic and Statistical Manual of Mental Disorders, 5th edition; ESS, Epworth Sleepiness Scale; FFS, Flinders Fatigue Scale; GAD-7, Generalised Anxiety Disorder assessment (7-item version); GBSS, Great British Sleep Survey; GSII, Glasgow Sleep Impairment Index; PHQ-9, Patient Health Questionnaire – 9- item version; PROMIS-10, Patient Reported Outcomes Measurement Information System, Global Health scale (10 items); QALY, quality-adjusted life-years; RAS, Relationship Assessment Scale; RCT, randomised controlled trial; SCI, Sleep Condition Indicator; SCNi, Sleep and Circadian Neuroscience Institute; SHE, sleep hygiene education; TAU, treatment as usual; WEMWBS, Warwick- Edinburgh Mental Well-being Scale; WPAI,SHP, Work Productivity and Activity Impairment questionnaire, Specific Health Problem; WSS, World Sleep Survey
